#### Rationale

Sirolimus (rapamycin) has the potential to restore mTORC1 balance by inhibiting its overactivation, which is commonly seen in aged muscles [29]. While mTORC1 is typically activated by branch-chain amino acids like leucine or by anabolic stimuli such as exercise, its chronic activation in older muscles leads to muscle atrophy rather than protein synthesis [29]. This atrophy is primarily due to the suppression of autophagy, highlighting the importance of mTORC1-regulated autophagy in aging muscle [29].

Weekly dosing with sirolimus (rapamycin) may provide alternating periods of mTORC1 activation (promoting protein synthesis) and inhibition (inducing autophagy), thereby improving muscle health. Given sirolimus (rapamycin)’s long half-life of 64 h in humans, weekly administration should be sufficient to create these beneficial cycles.

Combining exercise with weekly sirolimus dosing may offer synergistic benefits, enhancing muscle performance more effectively than exercise alone. This study aims to utilize a low-dose sirolimus protocol to balance therapeutic mTORC1 inhibition with minimal side effects, potentially offering a safe and effective strategy to boost muscle strength and endurance in the aging population.

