## Sample size {14}

The sample size was selected primarily to satisfy logistic constraints of this feasibility study. As this study is not confirmatory, we do not predicate the sample size primarily on power considerations: arm sizes of 20, assuming no withdrawals, will provide 80% and 90% power, respectively, to detect fairly large Cohen’s effect sizes of 0.8 and 0.9, respectively, at a nominal significance level of 0.1.

In regard to safety, the arm sizes and post-randomization follow-up time will enable to detect rate ratios of adverse events between the sirolimus (rapamycin) and placebo arms varying between 2.4 and 3.7, dependent upon the rate in the placebo arm and the dispersion of the data. Sample sizes of 12 per arm have been indicated as sufficient for pilot or feasibility studies [34]. However, our feasibility objective of variance estimation makes it preferable to aim for a total sample size of 40, as a 95% confidence interval for the variance will then have expected half-width of less than half the true variance, providing a reasonably precise estimate.

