Safety analysisSafety analysis set: this set includes all randomized participants. Adverse events will be allocated on an as-treated basis:◦ Events occurring before cessation of treatment or completion of the trial will be assigned to the randomized arm.◦ Events occurring after cessation will be assigned to the placebo arm.Analysis of adverse events:◦ Counts of adverse events will be regressed on the allocation arm as described above in interaction with the graded severity using negative binomial regression.◦ Dichotomized relatedness to the intervention (classified as possible, probable, or definite) will be regressed on the allocation arm using a quasi-binomial framework with logarithmic link (relative risk regression) or a relative risk working model (e.g., Poisson with bootstrap estimation of the variance) to test for non-inferiority of the rapamycin arm. Standard errors will be estimated using the bootstrap, resampling participants. The modalities of non-inferiority will be detailed in the final analysis plan.

Feasibility analysesScreening and randomization rates: overall and weekly screening and randomization rates will be reported with Poisson-based 95% confidence intervals.Cessation and withdrawal rates: rates of drug treatment cessation, exercise program cessation, and study withdrawal will be reported and compared across randomization arms using a log-rank test.Residual variance estimation: the residual variance of each outcome will be estimated to inform the sample size and analytical design of the phase 3 trial.

Adherence to medicationAdherence reporting: adherence to the medication will be reported by arm at 6 and 13 weeks using mean percentage of supply used and compared between arms using binomial regression with bootstrap-based standard errors and *p*-values [30].Causal effect estimation: the causal effect of the medication on the primary outcome will be estimated using two-stage residual inclusion estimation, with the randomized allocation as the instrumental variable [31].

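### Adverse events that start after a sirolimus participant stops treatment are counted in the placebo arm, with no lag window, so the safety comparison is no longer the randomised one and can understate harm

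*Protocol article*

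**What the plan says.** The safety set in section {20a} contains all randomised participants. Within it, "Adverse events will be allocated on an as-treated basis". Two rules follow: "Events occurring before cessation of treatment or completion of the trial will be assigned to the randomized arm", and "Events occurring after cessation will be assigned to the placebo arm".

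The main model then uses that assignment: "Counts of adverse events will be regressed on the allocation arm as described above in interaction with the graded severity using negative binomial regression". A second model regresses dichotomised relatedness on arm, "to test for non-inferiority of the rapamycin arm". For that test, "The modalities of non-inferiority will be detailed in the final analysis plan"; the transfer rule itself is not deferred. The article describes no adverse event comparison by arm as randomised, and no interval after the last dose during which events still count as on sirolimus. The Rationale describes the drug's "long half-life of 64 h in humans".

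**The concern.** The rule works in one direction. A placebo participant's events after stopping stay in placebo; a sirolimus participant's events after stopping leave the active arm and join the comparator. Stopping happens after randomisation and may depend on tolerability, so the two groups compared are no longer the randomised groups. With a 64 h half-life, an event a few days after the last dose can occur with drug still on board and yet be counted as a placebo event. A delayed harm would be counted the same way.

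Such events can arise. Section {20a} reports drug cessation separately from study withdrawal, section {11b} foresees discontinuation for adverse events, and section {18b} plans outcome collection after discontinuation.

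Safety and tolerability is the first secondary objective, and section {6b} justifies the placebo partly by the need to attribute adverse events correctly. A safety non-inferiority test is also planned, where a ratio pulled towards or below 1 makes it easier to declare sirolimus acceptable.

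**Working it through.** **The plan's own figure.** Section {14} gives detectable adverse event rate ratios of 2.4 to 3.7 with 20 per arm, but neither the placebo rate nor the dispersion. It cannot be reproduced from stated inputs, but it is plausible. Take log RR = (z_alpha + z_power) × √[(1/μ + k)/20 + (1/(μ·RR) + k)/20], with two-sided alpha 0.1 and 80% power. Then μ = 1, k = 0.5 gives 2.38, and μ = 0.5, k = 1.5 gives 3.70 (μ and k assumed).

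**Drug remaining after the last dose.** Fraction left = 0.5^(hours/64), assuming single-compartment decay:
- 3 days (72 h): 46%
- 7 days (168 h): 16%
- 14 days (336 h): 3%
- five half-lives = 5 × 64 = 320 h = 13.3 days

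**Effect of the transfer.** Let S and P be the sirolimus and placebo events, m the events moved, T the person-weeks per arm (20 × 13 = 260) and t the off-drug person-weeks moved.
- Counts only: (S − m)/(P + m). Any m > 0 lowers the ratio.
- Events and person-time moved: [(S − m)/(T − t)] / [(P + m)/(T + t)]. The direction depends on the post-stop rate.

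*Illustration 1 (assumed inputs).* S = 30, P = 15, ratio as randomised 2.0; 10% of sirolimus events moved, so m = 3.
- Counts only: 27/18 = 1.50.
- Person-time moved too, with the post-stop rate equal to the on-drug rate, so t = 26: (27/234)/(18/286) = 1.83. Here t = 26 corresponds, for example, to 4 of 20 participants stopping halfway (4 × 6.5 weeks).

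*Illustration 2 (assumed inputs).* One event per placebo participant over 13 weeks; on-drug rate ratio 2.0; 5 sirolimus participants stop at week 5. Off-drug time is 5 × 8 = 40 person-weeks and on-drug time is 220. On-drug events are 220 × 2/13 = 33.85; placebo events are 20.

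| Post-stop rate, × placebo | Events moved | As randomised | Rule, counts only | Rule, person-time moved |
|---|---|---|---|---|
| 0 | 0 | 1.69 | 1.69 | 2.31 |
| 1 | 3.08 | 1.85 | 1.47 | 2.00 |
| 2 | 6.15 | 2.00 | 1.29 | 1.76 |
| 4 | 12.31 | 2.31 | 1.05 | 1.43 |

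For the last row: as randomised (33.85 + 12.31)/20 = 2.31; counts 33.85/32.31 = 1.05; with person-time (33.85/220)/(32.31/300) = 1.43. With person-time moved, the rule's result passes from above to below the as-randomised ratio at a post-stop rate of about 1.4 times placebo.

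**Relatedness.** Assume analysis per event, 10 of 20 sirolimus events related against 5 of 20 placebo events (ratio 2.0), and 4 sirolimus events moved, r of them related. The ratio becomes [(10 − r)/16] / [(5 + r)/24]: 3.0, 2.25, 1.71 and 1.00 for r = 0, 1, 2 and 4. It can move either way.

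**The case against.** A reader might infer that the rule always favours sirolimus, or that the model ignores exposure. The article supports neither. Section {20a} is silent on person-time, section {14} speaks of rate ratios and follow-up time, and an offset is a detail that an article commonly leaves to the analysis plan. If off-drug time moves with the events, a low post-stop rate pushes the ratio up, against sirolimus.

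A reader might also infer a false protective effect. With 20 versus 20 events and 20% moved, counts alone give 16/24 = 0.67. With person-time moved at an equal post-stop rate the result is (16/208)/(24/312) = 1.00. Similarly, 30 versus 15 with 30% moved gives 21/24 = 0.88 on counts but (21/182)/(24/338) = 1.63 with person-time. Under that equal-rate assumption, 20% and 30% moved would correspond to about 8 and 12 of 20 sirolimus participants stopping halfway, for which the article gives no basis.

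Three further points stand. On the natural reading, an event that prompts stopping precedes cessation and stays in the randomised arm; only later-onset events move. Cessation and withdrawal are compared across randomised arms, so excess stopping on sirolimus would remain visible. The trial is described as not confirmatory, and if few participants stop, little changes.

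None of this justifies the transfer. A time-varying exposed/unexposed analysis is a recognised method, but it needs a carry-over window and matching exposure time, and it does not turn a former sirolimus participant into a randomised placebo control.

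**Conclusion.** The point holds. The transfer is explicit current text, it can move only sirolimus participants' events, and it has no lag despite the stated half-life. Followed as written, it gives up the randomised safety comparison and can place carry-over or delayed events in the comparator.

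On unadjusted counts, any moved event understates the sirolimus/placebo ratio. With person-time moved as well, the ratio is diluted when post-stop rates are high, as carry-over or delayed harm would produce, and can rise when they are low. Every size shown rests on assumed event counts, stopping patterns and post-stop rates. The article gives no cessation rate, event rate or dispersion, so the actual size cannot be derived, and outside unadjusted counts neither can the direction.

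**What to change.** Before unblinding, amend the safety analysis in section {20a} and carry the change into the analysis plan:

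- Delete the assignment of post-cessation events to placebo.
- Make the main analysis all events from randomisation to end of study by randomised arm (by product received if dispensed in error), with follow-up time accounted for in the negative binomial model.
- Use the same arm definition in the relatedness non-inferiority analysis.
- Make any on-treatment analysis supportive: events up to a pre-stated lag after the last dose (for example about five half-lives, roughly 14 days), with matching person-time. List later events separately as off-drug, never as placebo events.

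The cost is a change of wording and no new data collection. The downside is that some truly off-drug events stay in the sirolimus count; the supportive analysis shows how much they matter.

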## Trial design {8}

This study is a randomized, double-blind, placebo-controlled trial designed to evaluate the effects of once-weekly sirolimus (rapamycin) 6 mg on muscle strength and endurance in older adults participating in a thrice-weekly exercise program for 13 weeks. Randomization will be carried out using block randomization with stratification for age with a 1:1 allocation to receive either once-weekly sirolimus (rapamycin) or a placebo in addition to their exercise regimen. The primary, exploratory objective is to evaluate whether this combined intervention is at least equivalent to regular exercise alone in enhancing muscle performance in older adults.

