### Adverse event reporting and harms {22}

Plans for collecting adverse eventsAll adverse events (AEs) will be collected for this trial, including AEs leading to cessation or interruption of the study medication dosing schedule or interruption of the exercise program.Adverse events will be solicited during scheduled study visits and through spontaneous reports from participants.

Assessment of adverse eventsAn assessment will be made by the investigator or designee as to the severity and relatedness of the event.Severity will be classified as mild, moderate, or severe based on the impact on the participant's health and daily activities.Relatedness to the study intervention will be categorized as unrelated, possibly related, probably related, or definitely related.

Reporting of serious adverse events (SAEs)Any SAE, as defined by this protocol, starting at the time of randomization (day 0), is to be reported to the sponsor within 24 h of the site staff becoming aware of the event.Reporting will occur by completing the relevant page within the electronic case report form (eCRF) by the investigator or delegated individual.If the eCRF is not available at the time of the event, the investigator or delegated team member will contact the medical monitor directly.

Management of adverse eventsThe responsible investigator should institute appropriate diagnostic and therapeutic measures and keep the participant under observation for as long as medically indicated.Follow-up reporting of SAEs should continue until the event has resolved or stabilized.

Documentation and communicationAll AEs and SAEs will be documented in the participant’s medical records and reported in accordance with regulatory requirements.The sponsor will ensure that all relevant regulatory authorities and ethics committees are notified of SAEs as required by local regulations and guidelines.

Handling of unintended effectsAny unintended effects of the trial interventions or trial conduct will be reported and managed according to the same procedures as for AEs and SAEs.Regular safety reviews will be conducted by the data monitoring committee (DMC) to identify and address any emerging safety concerns promptly.

Protocol-specific detailsPeriodic monitoring visits will be conducted to ensure compliance with adverse event reporting requirements.A risk-based monitoring approach will be employed, combining on-site and centralized monitoring to ensure participant protection and data integrity.

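### The safety sample-size statement rests on one adverse-event rate ratio, but the only stated count model splits it into three severity-specific ratios; the total-count ratio should be the main contrast

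*Protocol article*

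**What the plan says.** In the protocol article, Sample size {14} says that the arm sizes and follow-up "will enable to detect rate ratios of adverse events between the sirolimus (rapamycin) and placebo arms varying between 2.4 and 3.7", the value being "dependent upon the rate in the placebo arm and the dispersion of the data". It mentions no severity grade and gives no power for these ratios.

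In Statistical methods {20a}, under Safety analysis, the one model for event counts is: "Counts of adverse events will be regressed on the allocation arm as described above in interaction with the graded severity using negative binomial regression". Adverse event reporting and harms {22} sets the grades: "Severity will be classified as mild, moderate, or severe based on the impact on the participant's health and daily activities".

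The next bullet in the safety analysis regresses relatedness on arm, with no severity split, to test non-inferiority. Only the details of that non-inferiority test are deferred to the final analysis plan. Safety and tolerability is the first secondary objective.

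**The concern.** When arm is crossed with a three-level factor, the arm coefficient is the rate ratio for the reference grade only, and each other grade has its own ratio. The article names no total-count ratio, averaged effect or joint arm test for counts. The natural reading of the sample size section is a single ratio for the total count, because it speaks of adverse events without qualification.

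If the plan is followed as written, events that are already sparse in 40 people are divided by grade before the arms are compared. The safety results would then be three estimates, each with a wider interval than the total count would give, and one of them may be undefined. Several overall summaries could be taken from the fit afterwards. They answer different questions, so the choice is better made before the data are seen.

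**Working it through.** **Inputs from the article.** 20 per arm with no withdrawals ("arm sizes of 20, assuming no withdrawals, will provide 80% and 90% power, respectively", stated for the efficacy effect sizes), 1:1 allocation, "at a nominal significance level of 0.1", and three severity grades.

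**Assumptions, because the article does not give them.** Two-sided test; 80% power for the rate ratio; placebo mean μ of 0.5 to 2 events per participant over follow-up; negative binomial dispersion k of 0.5 or 1, the same for each grade as for the total; the same true ratio in every grade; mild/moderate/severe split of 60/30/10% or 70/25/5%.

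**Formula.** SE(log RR) = √{[1/μ + 1/(μ·RR) + 2k]/20}. The detectable ratio solves log RR = (1.645 + 0.842) × SE. For one grade, μ is replaced by μ times that grade's share.

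**The plan's own figure.** The range 2.4 to 3.7 cannot be reproduced uniquely, because its placebo rate, dispersion, power and sidedness are not stated. A single two-arm contrast can give it: μ=1, k=0.5 gives 2.38; μ=3, k=1 gives 2.40; μ=0.5, k=1.5 gives 3.70; μ=0.25, k=0.25 gives 3.72. The range is therefore plausible for one ratio, and no error in it is shown.

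**Worked case, μ=1, k=1.** Total: SE = √[(1 + 1/2.77 + 2)/20] = 0.410, and exp(2.487 × 0.410) = 2.77. Severe at a 10% share (μ=0.1): SE = √[(10 + 10/7.6 + 2)/20] = 0.816, and exp(2.487 × 0.816) = 7.6.

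**Detectable ratios**

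| μ, k | Total | 60/30/10%: mild / moderate / severe | 70/25/5%: mild / moderate / severe |
|---|---|---|---|
| 0.5, 0.5 | 2.91 | 3.58 / 5.27 / 13.9 | 3.34 / 5.98 / 36.9 |
| 0.5, 1 | 3.30 | 3.98 / 5.72 / 14.7 | 3.74 / 6.45 / 38.4 |
| 1, 0.5 | 2.38 | 2.74 / 3.58 / 7.09 | 2.61 / 3.91 / 13.9 |
| 1, 1 | 2.77 | 3.13 / 3.98 / 7.60 | 3.00 / 4.32 / 14.7 |
| 2, 1 | 2.49 | 2.68 / 3.13 / 4.84 | 2.61 / 3.30 / 7.60 |

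Every grade-specific value exceeds the total-count value in its row. Of the ten row-by-split combinations, the mild ratio lies within 2.4 to 3.7 in eight, the moderate in three and the severe in none. The severe result depends on severe events being a minority. With an equal three-way split every grade would need 3.04 to 5.36, which is inside the range in two of the five rows.

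**In terms of estimation.** At μ=1, k=1, a true ratio of 2.77 and the 60/30/10% split, the 90% interval is the estimate multiplied and divided by exp(1.645 × SE). That factor is 1.96 for the total, 2.14 for mild, 2.56 for moderate and 4.28 for severe.

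**Simulation.** The Wald formula is unreliable when an arm expects one or two events, so the severe figures show direction rather than exact size. Gamma-frailty Poisson counts were simulated with 2,000 runs per setting, and a run without an estimable ratio was counted as no detection.

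| μ, k, true ratio, split | Power: total | Mild | Moderate | Severe | Severe ratio not estimable |
|---|---|---|---|---|---|
| 1, 0.5, 2.4, 60/30/10% | 83% | 70% | 51% | 13% | 16% |
| 1, 0.5, 2.4, 70/25/5% | 84% | 75% | 45% | 1% | 45% |
| 1, 1, 2.9, 60/30/10% | 85% | 78% | 61% | 19% | 15% |
| 1, 1, 2.9, 70/25/5% | 84% | 79% | 55% | 3% | 42% |

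The last column can be checked directly. The chance that an arm has no severe event is (1 + k·m)^(−20/k), where m is the mean severe count per participant. For the first row this is 1.05^(−40) = 0.142 on placebo (m=0.1) and 1.12^(−40) = 0.011 on sirolimus (m=0.24). So 1 − 0.858 × 0.989 = 15%, in line with the simulated 16%. Over all ten settings simulated (μ of 0.5 to 1.5), the severe ratio was not estimable in 5% to 69% of runs.

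**The case against.** Much of the case on the other side stands.

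- **The total count is an inference.** The sample size section does not say that its ratio is for all grades together. It ties the range to the placebo rate, and some mild and moderate rates also give values inside it. A reader might infer that the section and the model contradict each other, or that 2.4 to 3.7 is wrong. The documents show only a loose link between the two.
- **A reader might infer that no grade-specific ratio reaches the stated sensitivity.** The figures above refute this: mild ratios mostly do, and moderate ones sometimes do.
- **A reader might infer an inflated error rate from three tests at 0.1.** The count bullet names no test, and the plan puts estimation ahead of testing and calls the study non-confirmatory. A multiplicity argument would assume a procedure that the article does not state.
- **An overall effect can be extracted from an interaction fit,** and naming it is often left to the analysis plan. That limits the weight of the point but does not remove it. The article commits to a particular count model, and what it defers is the non-inferiority detail for relatedness.
- **Severity belongs in the safety objective, and the relatedness analysis already compares arms without a severity split.** Both are true. But relatedness is not the event rate ratio on which the sample size section relies.

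**Conclusion.** The point holds as a minor one. The sample size section supports safety with one between-arm ratio, most naturally for the total count, while the only count model stated leads directly to three grade-specific ratios. Under the assumed rates, dispersion and splits, each of these is less precise than the total-count ratio. In the simulated settings tabulated, power is 83% to 85% for the total, 70% to 79% for mild, 45% to 61% for moderate and 1% to 19% for severe events. With severe events at 5% or 10% of the total, the severe ratio lies outside 2.4 to 3.7 in every scenario tried and is often not estimable with 20 per arm. None of the rates, dispersions or splits comes from the article. The direction is more secure than the exact sizes.

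**What to change.** In the safety part of Statistical methods {20a}, name the total adverse-event rate ratio by arm as the main count contrast. Estimate it by negative binomial regression with log follow-up time as offset, and report it with the 75% to 95% intervals that the plan already uses for arm effects. Keep the arm-by-severity model as supportive and descriptive.

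The data layout must follow whichever arm-allocation rule the trial uses. If events after cessation are reassigned to placebo, as the article now states, one participant can contribute to both arms. Person-time must then be split in the same way, with standard errors from a bootstrap that resamples participants.

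The cost is a sentence or two and one further model, plus the person-time bookkeeping if the reassignment rule is kept. The drawback is that a total count weights mild and severe events equally, so the breakdown by grade must be shown beside it.

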### Procedure for unblinding if needed {17b}

Unblinding is permissible under specific circumstances where knowledge of the participant’s allocated intervention is essential for their safety and well-being. This may include serious adverse events where the clinical management of the participant requires knowledge of the treatment assignment.

In such cases, the following procedure will be followed:Initiation of unblinding request: the treating physician or investigator will determine the necessity of unblinding and initiate the request. The request must be justified and documented, explaining the medical need for unblinding.Consultation with the principal investigator: the principal investigator will review the request. If unblinding is deemed necessary, the principal investigator will proceed with the unblinding process.Unblinding process: the principal investigator will contact the designated third party (CompoundLabs) responsible for maintaining the randomization code. CompoundLabs will provide the treatment allocation information directly to the principal investigator.Documentation: the unblinding event, including the reason for unblinding, the date, and the personnel involved, will be documented in the participant’s case report form and study records.Participant withdrawal: once unblinded, the participant will be withdrawn from the study to maintain the integrity of the trial. The participant will continue to receive appropriate medical care as required.Notification: the relevant ethics committee will be notified of the unblinding event and provided with the necessary documentation.

By following this procedure, we ensure that unblinding is conducted ethically and only when absolutely necessary to protect the participant’s health and safety.

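### The adverse-event count model has no exposure term, and post-cessation events move to placebo without their time, so early stopping on sirolimus would pull the ratio towards safety

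*Protocol article*

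**What the plan says.** Sample size {14} sets the safety target in terms of rates and time: "the arm sizes and post-randomization follow-up time will enable to detect rate ratios of adverse events between the sirolimus (rapamycin) and placebo arms". The detectable ratio is put at 2.4 to 3.7 and is said to turn on how often placebo participants have events and on how dispersed the counts are. Neither value is given.

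The safety analysis in {20a} names response, predictors and family: "Counts of adverse events will be regressed on the allocation arm as described above in interaction with the graded severity using negative binomial regression". The arm in that sentence is the as-treated arm defined just before it. Events up to cessation belong to the randomised arm, and events after cessation belong to placebo. The analysis set is everyone randomised. No offset, exposure or person-time is mentioned, and the only item this safety text leaves to a later analysis plan is the detail of non-inferiority.

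Other sections allow follow-up to differ. Under {17b}, "once unblinded, the participant will be withdrawn from the study to maintain the integrity of the trial", and serious adverse events are the example trigger. Section {11b} also allows the investigator to withdraw a participant in that person's interest. The feasibility analyses in {20a} compare drug cessation and study withdrawal between arms.

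**The concern.** A count and a rate give the same arm ratio only if both arms are observed for the same time. Harm is one of the plan's own reasons for ending observation early, so a poorly tolerated drug could lose time at risk and, with it, counted events.

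The as-treated rule makes the gap sharper. Someone who stops sirolimus in week 4 and is followed to week 13 adds later events to the placebo count, while the nine weeks in which they arose are credited to no one. The placebo numerator grows and the sirolimus numerator shrinks, with both denominators unchanged. Safety is the first-listed secondary objective, and the error runs in the reassuring direction.

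**Working it through.** **The plan's own figure.** With n = 20 per arm, μ the expected placebo events per participant over full follow-up and k the dispersion, the Wald formula is log RR = (z_α + z_power)·√[(1/μ + 1/(μ·RR) + 2k)/n]. At two-sided α = 0.1 and 80% power the multiplier is 1.645 + 0.842 = 2.487.
- μ = 1, k = 0.5: RR = 2.38.
- μ = 0.5, k = 1.5: RR = 3.70.

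The stated range of 2.4 to 3.7 is therefore attainable, but μ and k are assumed, so it cannot be uniquely reproduced. The calculation gives all 20 per arm full follow-up.

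**Inputs for the bias (assumptions; the article gives no rates).** A fraction q of the sirolimus arm leaves or stops at fraction f of follow-up, with no placebo loss. The mean time on sirolimus is e = 1 − q(1 − f). R is the true rate ratio.

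**Early leaving, no offset.** Expected ratio = R·e.

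**Stopping but still observed, events reassigned, no offset.** Sirolimus events are proportional to R·e. Placebo events are proportional to 1 + (1 − e) if those who stop have events at the placebo rate. With the number randomised as denominator, the expected ratio = R·e/(2 − e).

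| q | f | e | Leaving, R = 2.4 | Reassignment, R = 2.4 |
|---|---|---|---|---|
| 0.10 | 0.50 | 0.950 | 2.28 | 2.17 |
| 0.10 | 0.25 | 0.925 | 2.22 | 2.07 |
| 0.20 | 0.50 | 0.900 | 2.16 | 1.96 |
| 0.20 | 0.25 | 0.850 | 2.04 | 1.77 |
| 0.30 | 0.50 | 0.850 | 2.04 | 1.77 |
| 0.30 | 0.25 | 0.775 | 1.86 | 1.52 |

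The last row is 2.4 × 0.775 = 1.86 and 2.4 × 0.775/1.225 = 1.52. For R = 3.7 the ranges are 2.87-3.52 and 2.34-3.35. In the last row a true 1.5 under reassignment becomes 1.5 × 0.775/1.225 = 0.95.

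**Some placebo loss.** With 20% against 5% leaving at half follow-up, the factor is 0.90/0.975 = 0.923 and 2.4 becomes 2.2. Equal leaving gives a factor of 1. Equal cessation does not remove the reassignment effect, because placebo events stay in placebo whether or not the participant has stopped.

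**With the split offset.** Sirolimus is R·e/e = R, placebo is (2 − e)/(2 − e) = 1, and the ratio is R again.

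**Data layout.** If each person who stops adds a second row to the placebo arm, the ratio without an offset is R·e(1 + q)/(2 − e). Over the table this runs from 1.97 to 2.39 for R = 2.4: the same direction, but smaller. Under that layout the direction reverses once f exceeds (1 + q)/(2 + q), for example 1.1/2.1 = 0.52 at q = 0.10. The article does not fix the layout.

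**Withdrawal triggered by events.** In a simulation with μ = 1, k = 0.5 and R = 2.4, each event led to withdrawal with the same probability in both arms. At probability 0.1 the ratio was 2.19 without an offset and 2.33 with one. At 0.2 it was 2.01 and 2.26.

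**The case against.** A reader might infer that the two sections contradict each other, or that the plan treats early leavers as fully observed. The article supports neither. Negative binomial regression takes counts as its response, its exponentiated coefficient is normally reported as a rate ratio, and an offset is often left to an analysis plan, which is not shown here. The point is that the stated model lacks a term, not that the plan rejects one.

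The loss of follow-up can also be overstated. Withdrawal after unblinding applies only when the allocation must be known for safety. Stopping treatment is not leaving the study, weekly contact is planned, and {18b} seeks final assessments from those who withdraw. The log-rank comparison is a feasibility measure and does not predict imbalance. All of this stands, and it makes the early-leaving bias conditional. But participants who stop and stay observed are exactly those whose events the plan moves to placebo. Good retention therefore brings that rule into play.

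Finally, precision is low. At μ = 1, k = 0.5 and R = 2.4 the standard error of log RR is √[(1 + 1/2.4 + 1)/20] = 0.35, so a 90% interval is about 1.35 to 4.25. The shifts in the table are 0.15 to 0.73 standard errors for leaving (0.051 to 0.255 on the log scale) and 0.29 to 1.32 for reassignment (0.100 to 0.458). Many are modest in a feasibility study, but they are systematic and free to avoid.

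**Conclusion.** The point holds as a cheap improvement. The model as specified does not estimate the rate ratio on which the safety target rests, and the reassignment rule makes person-time necessary. With those randomised as denominator, the error favours sirolimus if its participants leave earlier than placebo participants, or stop treatment and remain observed. Its size is unknown from the article. Under the assumed 10-30% at 25-50% of follow-up, 2.4, the smallest ratio the plan says it can detect, falls to about 1.9-2.3 or about 1.5-2.2 respectively. It is zero with equal exposure and no cessation. The reassignment figures also assume the placebo event rate after stopping.

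**What to change.** In the safety analysis of {20a}, add the log of person-time under adverse-event observation as an offset. Split each participant's time between treatment states by the rule already used for events, and use the same time for every severity row. Allow for clustering within participants; resampling participants, already planned for the relatedness analysis, would do this. Report the arm effect as a rate ratio, to match {14}.

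The cost is one model term plus dates of stopping treatment and of last adverse-event contact. The planned log-rank comparisons need cessation and withdrawal dates anyway, but their capture in the case report form should be confirmed. The offset assumes a constant event rate over follow-up and does not fully correct for withdrawal triggered by events, so observation time by arm should be reported beside the ratio.
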